#### Training and Supervision of Interventionist (Nurse Case Manager)

Training in the basic elements of the treatment algorithms and ongoing supervision and oversight of the case manager will be provided by the study physicians (a board certified endocrinologist and a board certified internist). Training will consist of two full days of didactic training on diabetes and hypertension in year 01 and then one day booster sessions in years 2-5 to maintain knowledge. In addition, the case manager will receive two full days of training on the FORA system and use of the secure website in Yr 01 and a full day of booster training in subsequent years. The nurse case manager will also participate in weekly research meetings to discuss challenging patients and resolve conflicts. The study physicians will be available by telephone at all other times to support the nurse case manager.

#### Treatment fidelity checks

In order to ensure that treatments are competently administered in accordance with the study protocol, a 20% random sample of intervention study charts will be reviewed along with the uploads from the secure site for the corresponding patients to ensure the case manager is adhering to the treatment algorithms. To evaluate adherence, rating forms will be developed based upon the treatment protocol to determine if the nurse case manager escalated treatment as appropriate and how well she accomplishes a range of relevant tasks for each patient. The study physicians will review and rate the randomly selected patient charts to assess for fidelity to treatment.

#### Patient adherence to treatment protocol

This is a very important aspect of this study given the intensity of the intervention protocol. We will adopt the following strategies to ensure an optimal level of compliance: (1) At enrollment, we will stress the importance of daily testing with the FORA system and daily upload of data; (2) We will place reminder telephone calls to participants on a weekly basis to remind them to test and upload data; (3) As described earlier, we will request the names and telephone numbers of three of the participant's friends and/or relatives who know how to reach the participant in the event we are unable to reach him or her; (4) The research staff will be flexible in accommodating participants' schedules and every attempt will be made to schedule research visits to coincide with clinic appointments. In addition, we will reimburse the participants ($25 each) for baseline, 3-, and 6-month follow-up visits.

#### Treatment enactment

The behaviors that are the target of this intervention are daily testing and uploading of blood glucose and blood pressure results from the FORA system. We will assess adherence to these behaviors based on review of frequency of uploads to the secure server.

### Primary Outcome Measure

The primary outcome is HbA1c level at 6 months of follow-up.

### Sample Size Determination and Power Analysis

For the continuous longitudinal clinical and quality of life outcomes for Primary Aims 1 and 2 (e.g., trajectory of HbA1C, BP, and SF-12 total scores), with 80 participants randomized 1:1 to each intervention group (TACM or UC), we will have 85% power to detect at least a 0.4 standardized (sd units) effect size between the TACM vs. UC intervention groups [assuming 3 time points (baseline, 3 and 6 months); intra-class correlation no greater than 0.6; level of significance (α) = 0.05, two-tailed ]. To account for dilution effect of ITT analyses and "administrative" dropout, i.e., those who drop out immediately upon randomization (do not receive a treatment or return for a post baseline visit), we inflated the sample size by 20% to achieve a final ITT sample size of 100 subjects randomized to each intervention group (N = 200).

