**Methods:**

We describe a four-year prospective, randomized clinical trial, which will test the effectiveness of technology-assisted case management in low income rural adults with T2DM. Two-hundred (200) male and female participants, 18 years of age or older and with an HbA1c ≥ 8%, will be randomized into one of two groups: (1) an intervention arm employing the innovative FORA system coupled with nurse case management or (2) a usual care group. Participants will be followed for 6-months to ascertain the effect of the interventions on glycemic control. Our primary hypothesis is that among indigent, rural adult patients with T2DM treated in FQHC's, participants randomized to the technology-assisted case management intervention will have significantly greater reduction in HbA1c at 6 months of follow-up compared to usual care.

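### The 85% power is stated for a three-visit trajectory that includes baseline, not for the declared primary outcome, HbA1c at 6 months

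*Protocol article*

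**What the plan says.** Protocol article, Primary Outcome Measure: "The primary outcome is HbA1c level at 6 months of follow-up". Study Aims & Objectives says the same. The primary hypothesis in the Abstract (Methods) is that intervention participants "will have significantly greater reduction in HbA1c at 6 months of follow-up compared to usual care".

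The only power statement, in Sample Size Determination and Power Analysis, has a different target: "For the continuous longitudinal clinical and quality of life outcomes for Primary Aims 1 and 2 (e.g., trajectory of HbA1C, BP, and SF-12 total scores"). It continues "with 80 participants randomized 1:1 to each intervention group (TACM or UC"), then "we will have 85% power to detect at least a 0.4 standardized (sd units) effect size between the TACM vs. UC intervention groups", with the bracketed conditions "assuming 3 time points (baseline, 3 and 6 months); intra-class correlation no greater than 0.6" and two-sided alpha 0.05. The 80 per arm is then raised to 100 for dropout and intention-to-treat dilution.

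The Statistical Analysis Plan subsection compares trajectories by mixed model and takes visit-specific comparisons, with 3 and 6 months as examples, from contrasts in that model. Its example covariates do not include baseline HbA1c.

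**The concern.** A power figure should describe the test that decides the trial. Here the deciding quantity is a difference at one visit (or a change to that visit), while the power is given for a longitudinal outcome over three visits, one of them taken before treatment starts.

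The condition on the correlation raises the same doubt. An upper limit on the intra-class correlation is a worst case for an average over visits, because highly correlated repeats add little information. For change from baseline, or for a 6-month value adjusted for baseline, the direction is reversed: power falls as the correlation falls. A limit of "intra-class correlation no greater than 0.6" then gives no protection.

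At stake is the trial's only sample-size justification. A reader would take it as 85% power for 6-month HbA1c, and that holds only under conditions the article does not state.

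**Working it through.** **Inputs** (Sample Size Determination and Power Analysis): n = 80 per arm, difference d = 0.4 SD, two-sided alpha 0.05, three visits including baseline, correlation r at most 0.6.

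**Assumptions added here:** the SD is that of one HbA1c measurement, r is the same between any two visits (compound symmetry), and a normal approximation is used.

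**Formula.** With V the variance of the per-patient summary in SD² units,

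power = Φ(d·√(n/(2V)) − 1.96) = Φ(2.530/√V − 1.96), since 0.4 × √40 = 2.530.

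**Step 1: the plan's own figure.** The mean of three visits has V = (1 + 2r)/3. At r = 0.6, V = 0.733 and power = Φ(2.954 − 1.96) = 84.0%. Exactly 85% would need 82.3 per arm, so the match is approximate. The other summaries at r = 0.6 lie further from 85%:

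| Summary | V | Power |
|---|---|---|
| Mean of all three visits | 0.733 | 84.0% |
| Mean of the two post-baseline visits, (1 + r)/2 | 0.800 | 80.7% |
| 6-month value alone | 1.000 | 71.6% |
| Change, baseline to 6 months, 2(1 − r) | 0.800 | 80.7% |
| 6-month value adjusted for baseline, 1 − r² | 0.640 | 88.5% |
| Post-baseline mean minus baseline | 0.600 | 90.4% |
| Post-baseline mean adjusted for baseline | 0.440 | 96.8% |

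The direction of the bound also fits an average: the three-visit mean has 90.4% power at r = 0.4 and 84.0% at r = 0.6, so 0.6 is its worst case. That calculation places 0.4 SD at every visit, whereas randomisation makes the expected baseline difference zero.

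**Step 2: the declared outcome.** Power for 0.4 SD at 6 months, 80 evaluable per arm:

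| Correlation r | Unadjusted (V = 1) | Change (V = 2(1 − r)) | Baseline-adjusted (V = 1 − r²) |
|---|---|---|---|
| 0.6 | 71.6% | 80.7% | 88.5% |
| 0.5 | 71.6% | 71.6% | 83.2% |
| 0.4 | 71.6% | 63.7% | 78.8% |
| 0.3 | 71.6% | 57.1% | 75.5% |

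**Step 3: what 85% requires.** 2.530/√V must reach 1.960 + 1.036 = 2.996, so V may be at most 0.713.

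- Unadjusted: V = 1 whatever the correlation, so 85% is never reached (113 per arm would be needed).
- Change: 2(1 − r) ≤ 0.713 gives r ≥ 0.644, outside the plan's bound (90 per arm would be needed at r = 0.6).
- Baseline-adjusted: 1 − r² ≤ 0.713 gives r ≥ 0.536, inside the bound (72 per arm suffice at r = 0.6).

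**Step 4: the inflation.** 80/(1 − 0.20) = 100 per arm. This is correct.

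**The case against.** The strongest reply is that the analysis is a longitudinal mixed model, so a longitudinal power calculation is appropriate. In part this stands: the model uses all visits and can deliver the 6-month comparison. But with complete data and separate baseline means for the two arms, its 6-month contrast is either the unadjusted difference (71.6%) or the difference in change (80.7% at r = 0.6). It gains the baseline-adjusted precision only if baseline is a covariate or the baseline means are constrained equal, and the article states neither.

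A second reply is that 100 per arm leaves slack. With all 100 analysed and no dilution, power at r = 0.6 would be 80.7% unadjusted, 88.5% for change and 94.2% baseline-adjusted. These are ceilings, because the plan reserves the extra 20 per arm for dropout and dilution.

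Some stronger readings are tempting but not supported:

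- **That 85% was certainly computed as a three-visit average.** The article names no formula, and the match is one point short. It is the closest of the variants tried and remains an inference.
- **That true power is about 50%.** That results from testing the three-visit mean with no effect at baseline (mean difference 0.8/3 = 0.267 SD, power 50.4%). No such test is planned.
- **That every correlation up to 0.6 leaves the trial short.** With baseline adjustment, 85% is reached from about 0.54 upward; without it, the 6-month comparison does not depend on the correlation.

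**Conclusion.** The point holds as a mismatch between the power statement and the primary outcome. The stated 85% is not the power of the 6-month HbA1c contrast under any of the three usual analyses at the plan's limiting correlation: 71.6% unadjusted, 80.7% for change, 88.5% baseline-adjusted. The upper bound on the correlation does not protect the latter two, and it excludes the value of about 0.64 that a change analysis would need.

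A reader might conclude that the trial is underpowered. The document does not show that: with baseline adjustment and a correlation of 0.54 or more, 80 evaluable per arm is enough. What is missing is a commitment to that adjustment and a lower bound on the correlation. The mismatch can be read directly from the text; the figures rest on compound symmetry, a single-visit SD as the unit, and 80 evaluable per arm. This should be fixed, but it does not call the sample size itself into question.

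**What to change.** Keep N = 200 and make three linked changes.

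1. In the analysis section, state that the 6-month HbA1c contrast adjusts for baseline HbA1c, either as a covariate or through a mixed model with baseline means constrained equal across arms.
2. In the sample-size section, restate power for that contrast. For example: with 80 evaluable per arm, two-sided alpha 0.05 and a 0.4 SD difference at 6 months, power is about 76, 79, 83 and 89% at baseline-to-6-month correlations of 0.3, 0.4, 0.5 and 0.6. Baseline should not be counted as an outcome visit.
3. Replace the upper bound on the intra-class correlation with the lower bound that 85% requires, a baseline-to-6-month correlation of at least 0.54.

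If baseline adjustment is not adopted, restate the power as about 72% for the 6-month value, or at most about 81% for change from baseline with correlation up to 0.6.

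The cost is a reworded power paragraph and one sentence on baseline handling. Baseline HbA1c is already collected, so no patients, visits or measurements are added. The stated power becomes conditional, and less favourable if the correlation is below 0.54.

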### Data Analysis

#### Preliminary Descriptive Analyses

Baseline values for demographic, clinical, and other putative prognostic variables will be compared for imbalance across the two treatment conditions (TACM; UC). These analyses will identify potential confounding variables to be used as covariates in subsequent analyses and will include race/ethnicity, gender, age, social support, health literacy, concurrent medical illness, depression, motivation etc. To investigate potential limits on generalizability, we will compare characteristics of the premature exits/protocol non-adherent with those who were completers/protocol adherent. Characteristics of participants who do not complete the study or do not comply with the treatment will be compared for both conditions.

#### Statistical Analysis Plan

The longitudinal trajectory of primary and secondary clinical (HbA1C, blood pressure) and quality of life outcomes will be compared using the generalized linear mixed models (GLMM) approach. In addition to accommodating a wide range of distributional assumptions [dichotomous/categorical (e.g., binomial), continuous (e.g., normal), ordinal, count (e.g., Poisson)], the approach accommodates missing data, time varying or invariant covariates, and multilevel data (clustering) such as repeated measurements on participants and possible cluster effects within clinics through inclusion of random effects in the model [27]. For the continuous outcomes such as blood pressure and HbA1C, GLMM is equivalent to a linear mixed effect model (MEM) approach. MEM analyses estimate individual change in outcome for each participant in addition to estimating average change in outcome within each intervention arm. Covariables, such as age, race, gender, medical comorbidity, social support, health literacy, and depression severity, will be added to the MEM model to adjust for putative confounding variables. For the dichotomous outcome, proportion (%) of participants who dropout prior to the 6-months end-of-study time point, we will compare proportion dropout for the TACM vs. UC intervention groups using GLMM for a binary outcome [equivalent to logistic regression analysis for the single end-of-study endpoint]. Appropriate contrasts will be specified to obtain individual time point comparisons of interest (e.g., 3 months, 6 months). Variables will be considered as fixed (e.g., primary intervention effect) or random (e.g., clinic) as appropriate.

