### Study Aims & Objectives

The primary objective of this study is to test the effectiveness of technology-assisted case management intervention using the FORA 2-in-1 and Telehealth System for diabetes in improving HbA1c levels in indigent, rural adult patients with type 2 diabetes treated in Federally Qualified Community Health Centers. The primary outcome will be HbA1c at 6 months post-randomization, while the secondary outcomes will be blood pressure control and quality of life at 6 months post-randomization.

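### HbA1c at 6 months is the single primary outcome, but the analysis section does not make the 6-month contrast the primary test or name baseline HbA1c as an adjustment, and the power text blurs primary and secondary outcomes

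*Protocol article*

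**What the plan says.** Three places in the article agree on the primary question.

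- Study Aims & Objectives: "The primary outcome will be HbA1c at 6 months post-randomization, while the secondary outcomes will be blood pressure control and quality of life".
- Primary Outcome Measure: "The primary outcome is HbA1c level at 6 months of follow-up".
- The Methods paragraph of the abstract hypothesises that intervention participants "will have significantly greater reduction in HbA1c at 6 months of follow-up compared to usual care".

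The analysis and power sections are worded differently.

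- Statistical Analysis Plan: "The longitudinal trajectory of primary and secondary clinical (HbA1C, blood pressure) and quality of life outcomes will be compared", by generalized linear mixed model, which for HbA1c is a linear mixed model. Later in the same section: "Appropriate contrasts will be specified to obtain individual time point comparisons of interest (e.g., 3 months, 6 months". On adjustment: "Covariables, such as age, race, gender, medical comorbidity, social support, health literacy, and depression severity, will be added to the MEM model". Baseline HbA1c is not in that list.
- Sample Size Determination and Power Analysis begins "For the continuous longitudinal clinical and quality of life outcomes for Primary Aims 1 and 2" and gives the trajectories of HbA1c, blood pressure and SF-12 as examples. It assumes three time points including baseline, an intra-class correlation of at most 0.6, two-sided alpha 0.05, and 80 per arm, for 85% power at 0.4 SD. The number is then inflated to 100 per arm.

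**The concern.** A trajectory comparison and a 6-month contrast are different tests and can give different answers. The section that fixes the analysis does not say which one decides the primary hypothesis, nor whether the 6-month comparison is of raw values, of changes, or of values adjusted for baseline.

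The treatment of baseline affects precision. Randomisation makes the expected baseline means equal in the two arms. A model that uses this, through a common baseline mean or through baseline HbA1c as a covariate, estimates the 6-month difference more precisely than a model that gives each arm its own baseline mean. The baseline value is collected on everyone, so not using it in this way would give up precision already paid for.

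The reference to primary aims in the power section adds a labelling conflict, because it covers two outcomes that the aims section calls secondary.

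**Working it through.** **Inputs.** From the power section: n = 80 per arm (100 after inflation), effect 0.4 SD, correlation ρ at most 0.6, two-sided alpha 0.05, visits at baseline, 3 and 6 months. Assumptions: equal correlation between all visits, a common SD, complete data, normal approximation, and no allowance for clinic.

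**Formula.** With v the variance of the estimand in units of the single-visit variance, power = Φ(0.4 / √(2v/n) − 1.96).

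**The stated 85%, at ρ = 0.6 and n = 80.** Two constructions come within about one point:

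- Arm difference in the mean of all three visits, baseline included: v = (1 + 2×0.6)/3 = 0.733, power 84.0%. This needs a 0.4 SD difference at baseline too. With true differences of 0, 0.4 and 0.4 the same test has 50.4% power, and with 0, 0.2 and 0.4 it has 31.5%.
- A 2-degree-of-freedom arm-by-visit test of the changes at 3 and 6 months, with 0.4 SD at both: 84.1%. With 0.2 at 3 months and 0.4 at 6 months: 71.8%.

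The article does not say which construction was used, if either. Neither is a 6-month contrast.

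**The 6-month contrast, at ρ = 0.6 and n = 80.**

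- Change from baseline, separate baseline means: v = 2(1 − 0.6) = 0.80. 0.4/√(1.60/80) = 2.83; Φ(0.87) = 80.7%.
- Baseline-adjusted or common baseline mean: v = 1 − 0.6² = 0.64. 0.4/√(1.28/80) = 3.16; Φ(1.20) = 88.5%.
- Raw 6-month difference, no use of baseline: v = 1. 0.4/√(2/80) = 2.53; Φ(0.57) = 71.6%.

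The variance ratio of change to adjusted is 0.80/0.64 = 1.25. For 85% power the change contrast needs 90 per arm and the adjusted one 72. At 100 per arm the powers are 88.5% and 94.2%, so the adjusted contrast with 80 per arm matches the change contrast with 100.

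If time were a linear term, three equally spaced visits would make the arm-by-time slope half the 6-month change per visit interval. The slope test would then be the change test.

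**Range of ρ.** The article gives 0.6 as an upper limit. The variance ratio is 2/(1 + ρ). Power at 80 per arm:

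| ρ | change | adjusted | variance ratio |
|---|---|---|---|
| 0.3 | 57.1% | 75.6% | 1.54 |
| 0.4 | 63.7% | 78.8% | 1.43 |
| 0.5 | 71.6% | 83.2% | 1.33 |
| 0.6 | 80.7% | 88.5% | 1.25 |

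For a mean over visits, a ceiling on ρ is the cautious choice, since that variance rises with ρ. For the change or adjusted 6-month contrast it is the favourable end.

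**The case against.** The strongest reply is that the article leaves the mixed model open. It does not say that baseline means are free in each arm or that time is linear. Counting baseline among three time points does not settle the matter, because a common-baseline model also uses baseline as an outcome visit. The covariate list is introduced as examples, and Preliminary Descriptive Analyses allows other baseline clinical variables to enter after an imbalance check, so baseline HbA1c is not excluded. Clinic is already foreseen as a random effect. Change-type and baseline-adjusted contrasts are both valid in a randomised trial, and model detail of this kind is often left to a separate analysis plan, which is not shown here. All of this stands, and it makes the precision loss conditional.

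Two stronger readings are tempting. A reader might infer that no 6-month contrast is planned. The section does plan one; it only fails to call it primary. A reader might also infer that any of several 5% tests could decide the trial. The abstract, the aims and the outcome section fix one outcome at one time, blood pressure and quality of life are secondary in the aims, and nothing lets a 3-month result count as success. A family error rate for such a rule would describe a trial other than this one.

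The reply does not remove the mismatch in what is written: the analysis section leads with a trajectory, and the power section contradicts the aims section on which outcomes are primary.

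**Conclusion.** The point holds as a mismatch between the declared endpoint and the stated analysis and power text, together with a free gain in precision. It is not an error that invalidates the trial. The mismatch is on the page. The loss applies only if the model is fitted in the ordinary way with separate baseline means: 25% more variance and 7.8 points of power at ρ = 0.6 and 80 per arm, rising to 15.1 points at ρ = 0.4. These figures rest on the assumptions listed in the working. The stated 85% does not match either the change or the adjusted 6-month contrast, so the power should be restated for whichever contrast is made primary. Whether a separate analysis plan already settles the model cannot be seen from the article.

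**What to change.** In the Statistical Analysis Plan section, state one primary test at two-sided 0.05: the TACM minus usual care difference in HbA1c at 6 months. Take it from the planned mixed model in one of two ways: baseline, 3 and 6 months as outcomes with a common baseline mean across arms, or 3 and 6 months as outcomes with baseline HbA1c as a covariate. Include clinic, the stratification factor, in the model. Describe the trajectory and 3-month comparisons as supportive.

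In the power section, list blood pressure and SF-12 as secondary, in line with the aims. Restate the power for the primary contrast with an assumed correlation between baseline and 6-month HbA1c, and show a range. With 80 per arm contributing and 0.4 SD, it runs from 75.6% at ρ = 0.3 to 88.5% at ρ = 0.6.

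The cost is wording and one recalculation. No visits, measurements or patients are added.
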